## Abstract

**Background:**

Australia’s health care system is under pressure. Pediatric referrals to public hospital emergency and outpatient departments have increased recently, overburdening emergency services and resulting in extended waiting times for nonurgent pediatric care. Children living outside metropolitan areas are disproportionately affected. Integrated models of care with pediatricians collaborating with general practitioners (GPs) in their practices have been evaluated in the United Kingdom and Australia. Results are promising for quality of care improvement and reducing referrals to hospitals. GPs and pediatricians found the model feasible, knowledge- and confidence-boosting. In-person pediatric-GP support is resource-intensive, limiting scalability and sustainability.

**Objective:**

The SUSTAIN trial is designed to evaluate a digitally delivered, integrated GP-pediatrician model of care. The primary objective is to determine whether the SUSTAIN model reduces GP referrals to hospital emergency departments for children <18 years. Secondary objectives include whether the model improves the delivery of guideline-concordant pediatric care by GPs, enhances GP confidence, and strengthens family trust in primary care. The trial also examines barriers and enablers to the implementation and includes a health economic evaluation comparing intervention costs with standard GP care.

**Methods:**

SUSTAIN uses a stepped wedge cluster randomized controlled trial design to implement a GP-pediatrician integrated model of care delivered digitally. Participating GP practices across metropolitan and nonmetropolitan New South Wales are included and randomly assigned a start time. The intervention consists of 12 months’ access to the shared GP-pediatrician consulting sessions with patients younger than 18 years conducted by telehealth, virtual pediatrician–led case discussions, phone/email pediatrician support, and complimentary access to the internationally renowned Sydney Child Health Program learning platform. GP and family surveys are collected at baseline and in the final month of intervention. An implementation evaluation using focus group discussions is conducted with each practice during the intervention and optional GP and family interviews at the end of the intervention. A health economic evaluation will explore the cost-effectiveness of this model of care.

**Results:**

The trial is supported through a 2.5-year New South Wales Ministry of Health Translational Research Grants Scheme. Human Research Ethics Committee approval was obtained in November 2022, and practice recruitment began in March 2023. Data collection commenced for all participating practices from September 1, 2023, with anticipated completion on February 28, 2025. Data analysis will commence from March 2025, with results expected in the first quarter of 2026.

**Conclusions:**

Positive outcomes for the SUSTAIN trial, demonstrating that virtual pediatric support for GPs in both metropolitan and nonmetropolitan areas can strengthen pediatric primary care provision, have the potential to influence future health policy. This innovative approach to integrated care could be rolled out across Australia and other countries with primary care–led health care systems facing similar challenges.

## Introduction

### Background

Demands on children’s tertiary health services in Australia and other high-income countries are growing [1]. Across Australia, children aged <15 years represent 26% of all lower urgency emergency department (ED) presentations and the highest presentation rates at ED [2]. While low urgency conditions do not necessarily equate with low severity or complexity [2], up to 74% of such presentations could be appropriately managed in a timely and safe manner within primary care [3]. High costs are involved in the hospitalization of children, both for governments and consumers. Alternative ways to strengthen pediatric primary care could avert some of the costs implicated in low-acuity presentations to hospitals [4,5].

Australia’s health care system is centralized around primary care provided by general practitioners (GPs). Over time, GPs have seen a diminishing proportion of pediatric cases, reducing their confidence in managing common pediatric conditions [6,7]. Adherence to clinical practice guideline recommendations by GPs has also been found to be reduced for some common conditions [8,9]. As the burden and complexity of disease evolve in high-income settings, increasingly, children present to general practice with medical complexity, including chronic diseases, neurodevelopmental, behavioral, and mental health issues [10-12]. The most common health system concerns expressed by GPs in Australia include an unsustainable workload in the context of this increasing patient complexity and difficulty navigating a fragmented health system [12]. These pressures impact the delivery of high-quality care, highlighting the need to better support GPs in fulfilling their vital role [13]. Challenges faced at the primary care level contribute to health inequities, especially for children living in rural and remote Australia, who experience reduced access and longer waitlists for specialist health services, contributing to diagnostic and treatment delays, adversely impacting health outcomes, and increasing health care costs [14,15].

The need for service redesign and exploration of new approaches to health care delivery for children, young people, and families has been identified to effectively manage health service demands. The primary care workforce requires support to improve care pathways for children, especially those with medical complexity and living in nonmetropolitan areas. Telemedicine and innovative technologies to support the sharing of clinical information have been highlighted as a mechanism to address this need [16].

Our group has implemented and evaluated an integrated GP-pediatrician model of care through several trials: the Strengthening Care for Children (SC4C), based on the UK Children and Young People’s Health Partnership [17], and Connecting Care for Children studies. These studies aimed to support GPs to strengthen the delivery of pediatric care, reducing unnecessary tertiary health service use and improving quality of care at the primary care level. In the UK setting, the intervention was implicated in a reduction in new patient hospital appointments, specialty referrals, and ED attendances, which was reported as a result. Families reported an increasing preference to see their GP, whilst GPs reported improved pediatric knowledge and understanding of how to navigate hospital services [18]. In Australia, the SC4C study, using an in-person, GP-pediatrician engagement model with pediatricians supporting GPs in their practices, demonstrated a reduction in referrals to hospital EDs and was found acceptable and suitable for GPs, pediatricians, and families [19]. However, the in-person model included considerable travel distances for pediatricians, even within metropolitan areas, posing equity and scalability challenges [20].

The evaluation design of the trial was discussed and piloted with GPs [19]. Although there was equipoise, one of the key areas discussed was the wish for all GPs to have access to the intervention. A stepped wedge randomized controlled trial (RCT) design was preferred to a 2-arm cluster RCT. The stepped wedge RCT design offers the gold standard of a cluster RCT. The advantage of a stepped wedge trial design ensures that all participating GP practices receive the intervention [21].

Building on learnings from the SC4C study, we propose to evaluate a model of integrated GP-pediatric care that uses a virtual approach to integrating GP-pediatric care, with the aim of demonstrating scalability and sustainability through a more equitably available model of care. The SUSTAIN study also evaluates the renowned Sydney Child Health Program (SCHP), a modular, web-based pediatric training program that has been developed for GPs, supported through the Sydney Children’s Hospital Network (SCHN) in New South Wales (NSW), and which has not previously been robustly evaluated [22].

### Objectives

Our primary and secondary objectives are to (1) reduce GP referrals to hospital ED and outpatient (OP) clinics for children and young people younger than 18 years and (2) improve GP pediatric care aligned with best practice (BP) guidelines, GP confidence, and increase family trust in primary care, while reducing family preference for specialist pediatrician referral.

Our implementation objective is to examine factors that help or hinder the implementation of SUSTAIN and understand factors associated with acceptability and scalability, and to assess the sustainability of the model.

Our economic objective is to assess the cost-effectiveness of SUSTAIN compared to that of standard GP care by undertaking a health economic evaluation (Table 1).

**Table 1. T1:** Trial objectives, data sources, data collection methods, and outcomes.

Primary and secondary objectives	Data sources	Methods of collection	Period of data collection	Outcomes of interest
What is the impact of SUSTAIN on GP^a^ referral to hospital OP^b^ clinics and EDs?^c^ (Primary Outcome)	Referral pop-up supported through GRHANITE technologies on GP desktop	GRHANITE data extraction of referral destination (including no referral) for each pediatric visit to participating GPs.	Collected as part of pediatric GP consults at the beginning of the control data period and throughout the intervention period.	Whether or not the GP referred the child to the hospital OP clinic or emergency department.
What is the impact of SUSTAIN on GP quality of care for common childhood conditions?	GP medical records	GRHANITE data extraction of care quality based on the measurement of the CareTrack Kids indicators.	Collected as part of pediatric GP consults at the beginning of the control data period and throughout the intervention period.	Whether or not the GP followed clinical guidelines (ie, they did not request unnecessary tests or prescriptions) for 5 common childhood conditions (ie, asthma/wheezing, bronchiolitis, constipation/abdominal pain, upper respiratory infections, and infant crying, and reflux).
What is the impact of SUSTAIN on GPs? (eg, confidence and skills in pediatric care and use of clinical guidelines)	GP web-based survey	Web-based control and intervention surveys completed by GPs via REDCap^d^.	Control surveys are collected in the month prior to the implementation commencing in each practice. Intervention surveys are collected in the last month of the implementation at each practice.	Changes in the level of confidence in pediatric care, level of knowledge and skill in navigating the health system for children, and reported use of clinical guidelines.
What is the impact of SUSTAIN on patients and family experience?	Family web-based survey	Web-based control and intervention surveys completed by families/caregivers via REDCap.	Control surveys are collected in the month prior to the implementation commencing in each practice. Intervention surveys are collected in the last month of the implementation at each practice.	Level of confidence in GP care, level of satisfaction with GP care, desire for referral to specialist care, and preference for GP or specialist review.
Health economic evaluation				
What is the cost of implementing the model of care? What is the cost- effectiveness?	Trial data and supplementary unit costings	Trial data on the model of care, health service activity, and combined with relevant unit costs.	Data will be collected throughout the model of care.	Costs of conducting the model of care compared with usual care and costs/cost offsets from changes in OP/ED referrals, MBS,^e^ and PBS^f^ (including out-of-pocket fees) compared with accessing usual care.
Implementation evaluation				
What are the aspects of the model of care that make it effective or ineffective at producing system change?	Pediatrician collected data, qualitative interviews, and web-based surveys with GPs, general practice managers and administration staff, trial pediatricians, families, and children	Consolidated framework for implementation research; qualitative interviews with families, children, and practitioners; web-based surveys. Pediatricians will collect unidentifiable data on the patient characteristics (eg, age and sex) and nature of pediatric support provided (eg, reason for consult and topic of case study discussion).	Interim qualitative data will be collected via focus groups with general practice 6 months into the model of care (iterative data collection process). Interviews with GPs, families, and pediatricians will be conducted at the end of the model of care. Web-based survey data will be collected upon completion of the model of care in each general practice; pediatrician data will be collected as part of the coconsultations, case study discussions, and phone/email support throughout the model of care.	Identify strategies for successful implementation as well as barriers and facilitators in adoption, delivery, and maintenance to inform future scaling. Describe the model of care, including number of children seen in GP-pediatrician coconsultations, reasons for coconsultations, number of and reason for phone and email support to the pediatrician, number and topic of case study discussions. Feasibility/acceptability and appropriateness of the model; adoption and fidelity to the model.
Sustainability				
Explore the sustainability and enduring effects of SUSTAIN post implementation on proportion of GP pediatric referrals to OP clinics or EDs and GP quality of care compared with preintervention GP care.	GP medical records	GRHANITE data extraction of referral destination (including no referral made) for each pediatric visit to participating GPs and of care quality based on the measurement of care provided for the 5 common childhood conditions.	Data will be collected on pediatric GP consults following completion of the model of care in each general practice (ie, once access to pediatrician support has ceased) until the end of the trial.	Whether or not the GP refers the child to a hospital OP or ED. Whether or not the GP followed clinical guidelines for 5 common childhood conditions (as above). How GP pediatric referrals (1) and quality of care (2) in the sustainability period compared with the intervention period (when the pediatrician was in the clinic). Economic evaluation results reflecting national rollout in real-world sustainable settings along with budget impact.

a GP: general practitioner.

b OP: outpatient.

c ED: emergency department.

d REDCap: Research Electronic Data Capture.

e MBS: Medicare Benefits Schedule.

f PBS: Pharmaceutical Benefits Scheme.

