### Intervention

SUSTAIN is a 12-month-long virtual model of care offered to all consenting GPs in participating general practices. It consists of four components: (1) virtual GP-led, shared GP-pediatrician consulting sessions with patients younger than 18 years, (2) virtual pediatrician-led case discussion sessions, (3) phone/email pediatrician support, and (4) complimentary access to the internationally renowned SCHP learning platform (Figure 2).

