#### GP Referrals

Data on GP referrals is not recorded in a standardized fashion in the GP EMR. Therefore, in order to measure the primary outcome, that is, referrals to hospitals, the GRHANITE team developed a tailored referral pop-up window (Section S5 in Multimedia Appendix 3) of common referral options to be completed by GPs following each pediatric consultation. This specific software extracts information regarding whether the GP referred a child and where (eg, no referral, hospital OP, or emergency department, private pediatrician, or allied health). The research team will continuously monitor GP data to promptly identify and address any technical issues posing a risk to data acquisition.

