#### GP Model of Care Engagements

As per our ethics approval, GP engagement with the components of pediatric support, such as coconsults, case discussion, phone/email, and SCHP access, will be recorded by the following processes and stored on the secure UNSW network drive. For coconsults, GPs will record deidentified patient information (age, gender, presenting problem, and reason for coconsult) via the SCHN Microsoft Bookings. For email, phone, and case discussions, pediatricians will record via REDCap each engagement, including GP name and deidentified patient information on the topic or concern discussed. For SCHP usage, the SCHP team will record the GP name and track GP access with the SCHP learning platform.

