### Sample Size Calculation

In the SC4C pilot study, there was a 7% reduction in GP referrals to hospital EDs and OPs, but we have powered our trial using a conservative 4% reduction [19,32]. The sample size of 18 practices with at least 60 pediatric consultations per practice per month will have 90% power to detect a 3.7% reduction (from the baseline rate of 10%) in the percentage of children who are referred to OP clinics or EDs following their GP appointment, assuming an intracluster correlation of 0.06 (derived from the pilot data [19]) and 2-sided type I error of 0.05. With the same sample size, we will have 80% power to detect a 5.5%‐6.55% reduction in the proportion of referrals to OP or ED for our planned stratification analysis by practice rurality, GP baseline referring level, years of practice, and gender.

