### Statistical Analysis

We will undertake descriptive analysis to describe the GP referral rate alongside the numbers of all children seen and the numbers of children referred to OP or ED by month during the study period for each practice.

All available data from each recruited GP and family will be analyzed according to an intention-to-treat principle. For the outcomes of GP referrals identified using the GP EMR data (eg, GP referral to OP clinic or ED), we will conduct mixed effects logistic regression, fitted to data collected during the control and intervention periods. The model will include a fixed effect of group (intervention vs control) and adjust for calendar time (as a continuous variable), and random effects to allow for variation in the outcomes for 3 hierarchical levels, including GP practice, GP within each practice, and patients seen by each GP.

Secondary outcomes collected at the child consultation level will be analyzed similarly, with separate models for the 5 common childhood conditions to measure quality of care. GP survey outcomes will be analyzed using mixed effects logistic regression, again including a fixed effect for group by intervention status and calendar time, and a random effect for GP practice, GPs, and patients.

We will control for baseline levels of GP referral for each practice in the analyses, GP-level factors (eg, rurality of the practice’s location, billing type, GP gender, years of practice, and number of children patients seen per week), and patient-level sociodemographic factors (eg, age at the encounter and socioeconomic status of residence). We will also consider whether the intervention effect varies by rurality of practice and GP-level factors (eg, referring level during baseline, years of practice, and GP gender) by the inclusion of interaction terms between group (intervention vs control) and these variables in the regression models.

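### The referral outcome is counted per visit, and co-consultations may add visits only under intervention, so the referral percentage can fall with the same children referred

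*Protocol article*

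**What the plan says.** **Unit of the outcome.** Table 1 under Objectives collects the primary outcome as "GRHANITE data extraction of referral destination (including no referral) for each pediatric visit to participating GPs". Under GP Referrals, the pop-up that supplies these data is "to be completed by GPs following each pediatric consultation". The Statistical Analysis section adds that "Secondary outcomes collected at the child consultation level will be analyzed similarly", which points to the consultation as the unit of the primary model as well. That model has random effects at "3 hierarchical levels, including GP practice, GP within each practice, and patients seen by each GP".

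**Unit in the sample size.** The Sample Size Calculation gives the target as a 3.7-point reduction from 10% "in the percentage of children who are referred to OP clinics or EDs following their GP appointment". The same sentence counts the sample as at least 60 pediatric consultations per practice per month.

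**Co-consultations.** The first intervention component is "virtual GP-led, shared GP-pediatrician consulting sessions with patients younger than 18 years". Table 2 places it in the embedding and intervention periods only. Under GP Model of Care Engagements, "For coconsults, GPs will record deidentified patient information (age, gender, presenting problem, and reason for coconsult) via the SCHN Microsoft Bookings", a booking system separate from the record extract. The Recruitment section mentions a practice poster promoting the service.

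**What is not stated.** The article does not say whether a co-consultation opens its own pop-up record, whether it adds to or replaces an ordinary visit, or how many are expected.

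**The concern.** The outcome is a proportion, and the intervention can act on its denominator as well as its numerator. Take a child seen at an ordinary visit, not referred, and booked for a co-consultation. If the co-consultation is recorded as another visit, that child supplies two records under intervention. If neither ends in a referral, both count as no referral. Under control, the same problem might have produced one record. The referral percentage then drops although exactly the same children are referred.

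Randomization and adjustment for calendar time do not protect against this, because the extra visits arise from the intervention. The patient random effect allows for correlation between a child's visits, but leaves a change in the number of visits per child in place. The listed sensitivity analyses deal with correlation structure, as-treated and per-protocol sets, actual start dates, contamination and noncompliance. None changes the unit or sets co-consultations aside.

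At stake are the primary estimate and the economic evaluation's cost per referral avoided, which is to be aligned with the statistical analysis.

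**Working it through.** **Inputs from the Sample Size Calculation:** 18 practices, at least 60 consultations per practice-month, baseline 10%, target reduction 3.7 points (to 6.3%), ICC 0.06, two-sided 5%, stated power 90%. **From Trial Design:** 3 practices switch each month (6 steps), with one embedding month excluded and then 11 intervention months. **From Results:** 18 calendar months. **Assumed, because not given:** the number of extra visits and the referral rate at them.

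**1. The plan's own figure.** This uses generalized least squares on practice-month means, with an exchangeable ICC and categorical month effects. Power = Φ(0.037/SE − 1.96).

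- 18-month layout, variance at the mean of the two rates: SE 0.01116; 0.037/0.01116 = 3.315; power 91.2%.
- Standard 7-period layout without a transition month, variance at 10%: SE 0.01172; 0.037/0.01172 = 3.157; power 88.4%.

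The stated 90% is therefore reproducible with 60 consultations as the unit. Other layouts and time codings give from about 71% to above 99%.

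**2. Dilution with the number of referrals unchanged.** With 60 visits and 6 referrals per practice-month and k extra visits, the percentage is 600/(60 + k).

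| k | Percentage | Fall (points) | Share of 3.7 |
|---|---|---|---|
| 1 | 600/61 = 9.84 | 0.16 | 4% |
| 3 | 600/63 = 9.52 | 0.48 | 13% |
| 6 | 600/66 = 9.09 | 0.91 | 25% |

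Because 60 is a minimum, a busier practice shows less. With 120 visits and 12 referrals, 6 extra visits give 1200/126 = 9.52%, a fall of 0.48 points.

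**3. Referral rate at the extra visits.** With f the extra visits as a share of usual visits and r the referral rate at them, the percentage is (0.10 + f·r)/(1 + f). At f = 10%:

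- r = 0: 9.09%, a fall of 0.91 points.
- r = 5%: 0.105/1.10 = 9.55%, a fall of 0.45.
- r = 10%: 0.110/1.10 = 10.00%, no change.
- r = 20%: 0.120/1.10 = 10.91%, a rise of 0.91.

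**4. What would produce the whole target.** With r = 0, 0.10/(1 + f) = 0.063 gives f = 58.7%. That is 0.587 × 60 ≈ 35 extra visits per practice-month, or about 634 a month over 18 practices.

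**5. Chance of a significant result from dilution alone (r = 0, nominal 5%).** With z = fall/SE, and SE scaled to the mean of the two rates, the probability is Φ(z − 1.96) + Φ(−z − 1.96). With categorical months, over the two layouts in step 1:

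- f = 2%: about 5%.
- f = 5%: about 7%.
- f = 10%: about 12%. In the 7-period layout SE = 0.01172 × √(0.0863/0.09) = 0.01148, and z = 0.00909/0.01148 = 0.79.
- f = 20%: 29% to 32%.

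The article plans calendar time as a continuous variable. Under a linear trend in the 18-month layout, the SE at 10% is 0.00893. At f = 10% it scales to 0.00875, z = 1.04 and the probability is about 18%.

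**The case against.** **The extra visit is a scenario.** Nowhere does the article say that a co-consultation adds a visit or is logged in the referral pop-up. The poster promotes the service to patients, so a co-consultation could be a first contact or stand in for a review visit. This stands, and it makes the point conditional. A reader might infer that the percentage is bound to fall, or that the outcome has a built-in bias towards benefit. The article supports neither inference. Separate booking makes an added visit plausible, no more, and the children concerned may be ones with an above-average chance of referral, which would shrink or reverse the artefact.

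**The size is assumed and mostly small.** This also stands. The case shown uses the minimum of 60 visits and no additional referrals. A reader might suppose that dilution could create the whole target effect. About 634 extra visits a month from one full-time-equivalent pediatrician, who also provides case discussions and phone/email support, is implausible as a matter of judgment, though the article gives no capacity figure.

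**The sample-size wording is loose.** A reader might conclude that the trial was sized on a different quantity. The same sentence counts consultations, and the stated power reproduces with them, so that conclusion is not supported. What remains is that the article describes the outcome both per visit and per child.

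**The shift would be visible, and counting rules belong in the SAP.** Monthly counts of children seen and children referred are to be described for each practice, and co-consultations are logged. This helps detection, but it leaves the primary estimate uncorrected. A counting rule may well exist in a fuller document. The article, however, itself fixes the unit, and does so in two ways, so this is not merely an omitted detail.

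**Conclusion.** The concern holds in conditional form. As written, the outcome is counted per visit, a component found only under intervention may add visits, and no stated rule or sensitivity analysis prevents the referral percentage from falling with the same children referred.

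On the stated minimum of 60 visits, the fall would be 0.16 to 0.91 points for 1 to 6 extra visits per practice-month. This rests on three assumptions: those volumes, co-consultations being recorded as additional visits, and no additional referrals arising from them. If any of these fails, the artefact shrinks, vanishes or changes sign. In every case where visits are added, the estimate mixes referral behavior with visit frequency, and that is reason enough to settle the unit before analysis. It should be resolved, but it does not show that a positive result would be spurious.

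**What to change.** Use one unit in Table 1, GP Referrals, the Sample Size Calculation and Statistical Analysis. The preferred unit is one record per child per episode, for example 30 days from the index visit, coded 1 if any outpatient or ED referral was made within it. A co-consultation inside that window then joins its index visit and adds no denominator unit. A calendar-month unit would not achieve this, because an index visit late in one month and a co-consultation early in the next would still count twice. State also how an episode that crosses a period boundary is assigned, for instance by the date of the index visit.

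Report the per-visit analysis alongside. If the per-visit outcome stays primary, prespecify the child-episode analysis as a sensitivity analysis. In either case, state whether co-consultations generate pop-up records.

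**Cost.** No new data are needed: the Data Management Plan already provides a project ID unique to each patient, so this is wording and a data-collapse step. There will be fewer analysis units than visits, by an amount that cannot be judged because visits per child are not given. The 10% baseline, the ICC of 0.06 and the 60-per-month figure must be restated for the chosen unit. A co-consultation more than 30 days after the index visit would still open a new episode, so the window length needs a reason.
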